#### Changes in hormonal/metabolic parameters

Hormonal/metabolic profiles will be determined at the baseline visit and the end-of-treatment visit. The mean values of changes in hormonal/metabolic parameters before and after treatments will be used in the primary analysis.

#### Changes in QOL scores

QOL scores will be assessed by the SF-36, PCOS-QOL, ChQOL, PSQI, Zung SAS, and Zung SDS questionnaires. The participants will complete the questionnaires at the baseline visit and again at the end-of-treatment visit. Higher scores on the SF-36, PCOS-QOL, and ChQOL questionnaires indicate better function, whereas higher scores on the PSQI indicate poorer sleep quality, and higher scores on the Zung SAS/SDS indicate worse anxiety/depression. The mean changes in QOL scores of each group will be used in the analysis.

#### Adverse events

All AEs will be categorized, and the percentage of patients experiencing AEs and serious adverse events (SAEs) during the treatment period and follow-up period will be documented and reported. For fetuses, SAEs and AEs will be reported as those occurring after 20 weeks of gestation through birth, and for newborns, SAEs and AEs will be reported as those occurring within 28 days after birth. SAEs will include events that are fatal or immediately life-threatening, severely or permanently disabling, or that require hospitalization; overdoses (intentional or accidental); congenital anomalies; pregnancy loss after 12 weeks of gestation; neonatal death up to 6 weeks after delivery; or any event deemed to be serious by the site PIs. The Data and Safety Monitoring Board (DSMB) will review AEs on a quarterly basis and will review SAEs immediately.

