## Objectives

The objectives of the present trial are to test the following four hypotheses:
Letrozole is more likely than personalized acupuncture to induce ovulation and to result in live birth.Personalized acupuncture is more likely than fixed acupuncture to induce ovulation and to result in live birth.Fixed acupuncture is more likely than placebo letrozole to induce ovulation and to result in live birth.Personalized acupuncture is more likely than letrozole, fixed acupuncture, and placebo letrozole to reduce the miscarriage rate and the risk of pregnancy complications.

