### End-of-treatment visit

The end-of-treatment visit will be performed when the women conceive or finish four cycles of treatment. Baseline measures will be repeated in all subjects, including vital signs, height, weight, hip, and waist measurements; hirsutism and acne assessments; sex hormone steroids (FSH, LH, and total T for women who are not pregnant and β-HCG, P, E2, and total T for women who are pregnant); SHBG; metabolic profile (glucose and insulin concentrations, HbA1C, C-peptide, cholesterol, triglycerides, HDL-C, and LDL-C); liver profile (AST, ALT, and total bilirubin); and renal profile (BUN and creatinine). Subjects will return menstrual and intercourse journal logs, and their AEs and concomitant medications will be recorded. Fasting blood samples will be obtained, and TCM syndrome diagnosis and the SF-36, PCOS-QOL, ChQOL, PSQI, Zung SAS, and Zung SDS questionnaires will be repeated.

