### Pregnancy visit (only with conception)

Serum progesterone and β-HCG levels will be determined at local sites to document ovulation and pregnancy. A serum β-HCG > 10 IU/L will indicate pregnancy, and in pregnant women, the serum β-HCG level will continue to be checked on a weekly basis. Pelvic ultrasound will be performed to determine the location and number of fetuses when the serum β-HCG is 2000–4000 IU/L. Pelvic ultrasound will then be performed every 2 weeks until viability of the pregnancy is determined by visualization of fetal heart motion.

Women who conceive will be referred to their prior or referring doctors for antenatal care at around 10–12 weeks of gestational age. Subsequent arrangements will be performed at weeks 18–24, 32, and 36 or upon the prescription of the obstetrician. In the present trial, pregnant women who present with threatened miscarriage or who are considered to have a significant risk for miscarriage can be given oral Duphaston (10 mg three times per day; Solvay Pharmaceuticals B.V., Veenendaal, the Netherlands) until 12 weeks of gestation or until 1 week after the vaginal bleeding stops. This information will be documented in the study records. No other medications, including HCG, herbal medications, or acupuncture, will be given.

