### Follow-up of pregnancies

Women who conceive will be referred to their prior or referring doctors for antenatal care at around 10–12 weeks of gestational age, and they will be seen in follow-up until delivery or termination of gestation. All pregnancies (including multiples) will be followed to monitor weight, glucose tolerance, blood pressure, and fetal growth and to determine the pregnancy outcomes. Glucose tolerance will be measured by oral glucose tolerance test in all pregnant women at 24–28 weeks of pregnancy. Women will be instructed to inform the study personnel of the outcomes of the pregnancy, and we will obtain delivery records from the obstetricians to determine the birth weight, length of gestation, and any prenatal complications in the mother or neonatal complications in the infant. Phone contacts will be initiated if the pregnant woman has not contacted the study personnel within 6 weeks of the original estimated date of childbirth.

We will collect pregnancy outcome data and track the outcomes of all women who have a positive serum pregnancy screen during the course of this study. We will record biochemical pregnancies (defined as positive serum pregnancy screens without ultrasonically detected pregnancies), ectopic pregnancies, and all intrauterine pregnancy losses both before and after 20 weeks, including miscarriages, abortions, fetal deaths, and stillbirths.

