The analysis of secondary (supplemental) outcomes measured over time will entail the application of statistical methods that have been developed for correlated data because repeated observations will be made over time for each individual. For secondary outcomes such as hormone levels, a linear mixed-effect model will be fit where the main independent variables will be treatment group, time, and their interaction as well as the designed randomization stratification factors as covariates. Logistic regression models will be used in secondary analyses to evaluate the predictive value of treatment arm, clinical site, body mass index, and other explanatory variables on binary outcomes (e.g., live birth, abortion). Cox proportional hazards models and the Kaplan-Meier method will be used to compare time to pregnancy in the treatment groups. Effects on QOL, as determined by the change from baseline physical and mental component scores, will be analyzed by univariate and multivariate ANCOVA. The adequacy of blinding will be tested by Fisher’s exact test comparing true group assignments with participant guesses, including “don’t know.” In order to evaluate acupuncture as a unique therapy, the combination of the personalized acupuncture group and fixed acupuncture group will also be compared with the combination of the letrozole and placebo letrozole groups for the analysis of primary outcome. Differences in AE rates will be analyzed in a negative binomial generalized linear model. A *P* value < 0.05 with a two-tailed test will be considered significant. All statistical analyses will be performed using IBM SPSS Statistics version 21.0 software (IBM Corp., Armonk, NY, USA).

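### AE and SAE percentages cover treatment and follow-up, but only women who conceive are followed after treatment; if the two periods are combined, SAE percentages track the conception rate

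*Protocol article*

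**What the plan says.** The Adverse events section fixes one summary for the women: "the percentage of patients experiencing AEs and serious adverse events (SAEs) during the treatment period and follow-up period will be documented and reported". It does not say whether the two periods are shown together or apart, or which women form the denominator.

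The second period exists only for some women. Under End-of-treatment visit, "The end-of-treatment visit will be performed when the women conceive or finish four cycles of treatment". The pregnancy visit is restricted to women who conceive, and under Follow-up of pregnancies, "they will be seen in follow-up until delivery or termination of gestation". No contact after the end-of-treatment visit is described for the others. Table 3 places AE assessment at the treatment, end-of-treatment and pregnancy visits only. Under Intervention, treatment stops once a woman is pregnant.

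The SAE list includes "congenital anomalies; pregnancy loss after 12 weeks of gestation; neonatal death up to 6 weeks after delivery", and also events that are "severely or permanently disabling, or that require hospitalization". Fetuses (after 20 weeks through birth) and newborns (28 days) have reporting windows of their own; the women have no such split.

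For the comparison between arms, Data analysis says only: "Differences in AE rates will be analyzed in a negative binomial generalized linear model".

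**The concern.** Whether a woman enters the second period depends on conception, which lies on the path to the primary outcome and is expected to differ strongly between arms. A woman who conceives is observed for many more weeks and is exposed to events that a woman who does not conceive cannot have. If both periods go into one percentage per woman randomized, arms with identical underlying risks show different SAE percentages, and the more effective arm shows more. An SAE excess for letrozole over placebo could then be read as toxicity when it only reflects more pregnancies. The DSMB, which reviews AEs quarterly and SAEs immediately, could be shown the same pattern.

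**Working it through.** The protocol gives no expected AE or SAE rate, so there is no safety figure to reproduce.

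**Inputs from the protocol article.** Planned live birth rates of 35% (letrozole), 25% (personalized acupuncture), 15% (fixed acupuncture) and 5% (placebo letrozole), and 275 women per arm (Sample size calculations); up to 16 weeks of treatment (Intervention).

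**Assumptions, identical in every arm.** Background SAE risk *b* = 1–2%; SAE risk per pregnancy *s* = 5–30%; share of conceptions lost 15–30%.

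**Step 1: simple case.** Use the live birth rate *p* as a lower bound for the proportion pregnant, with *b* = 1% and *s* = 15%. SAE percentage over both periods = *b* + (1 − *b*) × *p* × *s*.

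| Arm | Calculation | SAE % | Of 275 |
|---|---|---|---|
| Letrozole | 0.01 + 0.99 × 0.35 × 0.15 | 6.2 | 17 |
| Personalized | 0.01 + 0.99 × 0.25 × 0.15 | 4.7 | 13 |
| Fixed | 0.01 + 0.99 × 0.15 × 0.15 | 3.2 | 9 |
| Placebo | 0.01 + 0.99 × 0.05 × 0.15 | 1.7 | 5 |

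The letrozole:placebo ratio is 6.20/1.74 = 3.6 with no true difference in risk.

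**Step 2: wider range.** Put conception at *c* = *p*/(1 − loss) and the SAE percentage at 1 − (1 − *b*)(1 − *c* × *s*).

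- Smallest ratio (loss 15%, *b* = 2%, *s* = 5%): letrozole 1 − 0.98 × (1 − 0.412 × 0.05) = 4.0%; placebo 1 − 0.98 × (1 − 0.059 × 0.05) = 2.3%; ratio 1.8 from unrounded values.
- Largest ratio (loss 30%, *b* = 1%, *s* = 30%): letrozole 1 − 0.99 × (1 − 0.50 × 0.30) = 15.8%; placebo 1 − 0.99 × (1 − 0.071 × 0.30) = 3.1%; ratio 5.1.

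The order is letrozole, personalized, fixed, placebo throughout. Holding *b* fixed ignores that women who conceive stop treatment early. If their treatment exposure is halved, the smallest case becomes 0.412 × [1 − 0.98^0.5 × 0.95] + 0.588 × 0.02 = 3.6% against 0.059 × [1 − 0.98^0.5 × 0.95] + 0.941 × 0.02 = 2.2%, a ratio of about 1.6. The order is unchanged.

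**Step 3: would an offset for total time be enough?** Assume conception at week 8 and 38 weeks to birth. Mean weeks observed are 0.65 × 16 + 0.35 × 46 = 26.5 for letrozole and 0.95 × 16 + 0.05 × 46 = 17.5 for placebo, a ratio of 1.5. Dividing the step 1 ratio by this leaves roughly 3.56/1.51 = 2.4. Total time does not correct for events that need a pregnancy.

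**Step 4: AEs of any kind.** Let *a* be the AE risk over 16 weeks of treatment, *f* (0.5–0.6) the fraction of treatment received by women who conceive, and *q* (10–50%) the AE risk in pregnancy. The percentage is *c* × [1 − (1 − *a*)^*f* × (1 − *q*)] + (1 − *c*) × *a*. At 30% loss (*c* = 0.50 for letrozole, 0.071 for placebo), letrozole minus placebo is:

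- *a* = 40%: 35.1 − 39.3 = −4.2 points (*f* = 0.5, *q* = 10%) to 51.6 − 41.7 = +9.9 points (*f* = 0.6, *q* = 50%).
- *a* = 60%: −7.3 to +4.8 points at the same two settings.

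The sign is not fixed.

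**Step 5: periods separated.** With the step 2 inputs, the treatment-period percentage is *b* in every arm and the percentage among women who conceive is *s* in every arm, so the artefact disappears. Shorter treatment in women who conceive leaves a small residue: with *b* = 1% and half exposure (0.5%), letrozole 0.50 × 0.5 + 0.50 × 1 = 0.75% against placebo 0.071 × 0.5 + 0.929 × 1 = 0.96%. A log-time offset within the treatment period removes it.

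**The case against.** The strongest reply is that the protocol nowhere says the periods are merged. The sentence names two periods and can be met by two columns. Denominators, table layout and a model offset are commonly left to the analysis plan, which is not shown, and a negative binomial model can carry an offset. This stands in part: combination is an inference, though the natural one, since a single percentage of patients is stated with no split for the women. An offset for total time would not be a cure (step 3).

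Second, fetal and newborn events have their own windows, so congenital anomaly and neonatal death need not enter the women's percentage. That stands. Pregnancy loss after 12 weeks starts before the fetal window opens at 20 weeks, however, and admissions during pregnancy belong to the woman, so pregnancy-only SAEs remain.

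Third, the size rests on assumed risks, and the protocol specifies no significance test of SAE percentages. A two-proportion test at 275 per arm would be significant in about 79% of trials under step 1, but that test is not in the plan and the figure is only an illustration.

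Fourth, hypothesis 4, that personalized acupuncture will "reduce the miscarriage rate and the risk of pregnancy complications", might seem to gain false support: with equal risk per pregnancy, complications per woman randomized would show 25/35 = 0.71 against letrozole. That depends on a denominator the document does not state. Pregnancy loss, part of the same hypothesis, is explicitly measured among women who conceive.

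Fifth, DSMB stopping refers to AEs caused by the study medications, which is a causal judgement; nothing shows that the board would act on a crude percentage.

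**Conclusion.** The point holds in conditional form. If the treatment and follow-up periods are combined per woman randomized, SAE percentages are confounded with conception. Under the plan's live birth rates and equal underlying risks, the more effective arms show more SAEs: 6.2/4.7/3.2/1.7% in the worked example, with a letrozole:placebo ratio of about 1.8 to 5.1 over the wider range. All SAE risks and loss shares are assumptions; real differences in treatment-period SAEs could change the order. This is more than missing detail, because the stated summary and model, applied as written, make the comparison depend on an intermediate step of the primary outcome.

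A reader might infer that the best arm will look least safe on all AEs. The protocol does not support that: treatment stops at conception, and the difference for AEs of any kind can be nil or reversed (step 4). Nor does the text adopt the reading that admission for delivery is an SAE. It leaves the classification open; counting each one would give about 36/26/16/6% (for letrozole, 0.01 + 0.99 × 0.35), so it is worth settling.

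**What to change.** - Make the between-arm safety comparison on treatment-period AEs and SAEs, from the start of treatment to the positive serum HCG or the end-of-treatment visit, in all randomized women, with log observed time as offset in the negative binomial model.
- Report maternal pregnancy-period events in a separate table, per woman who conceives and per woman randomized. The first denominator is a subgroup formed after randomization and the second carries the conception rate, so neither alone should be read as toxicity of an intervention.
- Keep the existing fetal and newborn windows.
- State how admission for delivery is classified.
- Give the DSMB the same split.

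The cost is wording and one extra table. Conception and delivery data are already collected.

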### Sample size calculations

In previous studies, the overall live birth rate for infertile women with PCOS who received letrozole for 6 months was 36.3% [28], whereas for women who received fixed acupuncture twice per week with a maximum of 32 acupuncture treatments, the overall live birth rate was 13.9% [10]. Thus, we hypothesize that the live birth rate is 35% for four cycles of letrozole treatments and 15% for fixed acupuncture three times per week. We have chosen 10% as the minimal clinically detectable difference that is likely to change clinical practice. Assuming a 35% live birth rate with letrozole, a 25% live birth rate with personalized acupuncture, a 15% live birth rate with fixed acupuncture, a 5% live birth rate with placebo letrozole, and an 80% power at a significance level of 0.05, we calculated that 250 subjects per treatment group were required. The sample size was increased from 250 to 275 per group considering a 10% dropout rate, and thus 1100 women in total will be enrolled.

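### The single 80% power figure does not hold for letrozole 35% versus personalized acupuncture 25%: 250 per group gives about 68.5%, and 329 per group would be needed

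*Protocol article*

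**What the plan says.** Sample size calculations takes 10 percentage points as the smallest difference that matters and sets the four arms on an evenly spaced ladder: "Assuming a 35% live birth rate with letrozole, a 25% live birth rate with personalized acupuncture", then "a 15% live birth rate with fixed acupuncture, a 5% live birth rate with placebo letrozole". One size and one power are attached to the whole ladder: "and an 80% power at a significance level of 0.05, we calculated that 250 subjects per treatment group were required". The 250 is raised to 275 per group for 10% dropout, which gives 1100 women in total.

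Objectives makes each step of the ladder a hypothesis on live birth. The first listed is "Letrozole is more likely than personalized acupuncture to induce ovulation and to result in live birth"; the next two are personalized over fixed acupuncture and fixed acupuncture over placebo letrozole. The list carries no formal ranking. Data analysis names the Pearson chi-square test for the primary outcome, and a P value below 0.05 "with a two-tailed test will be considered significant".

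**The concern.** A fixed 10-point gap does not need the same number of women at every point on the scale. The variance of a proportion grows towards 50%, so 35% versus 25% needs more women than 25% versus 15%, and 15% versus 5% needs fewer. One group size with one power figure therefore cannot describe all three steps, and a size meant to cover all of them must come from the most demanding pair.

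At stake is how the letrozole versus personalized acupuncture result is read. The article says that the findings will bear on whether personalized acupuncture can serve as an alternative treatment, and its Background calls letrozole first-line. If letrozole is truly 10 points better, the article's 80% implies a 20% chance of missing that. If the true power is lower, a reader who trusts the stated figure will give a non-significant result on this contrast more weight than it deserves.

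**Working it through.** **Inputs, all from the protocol article.** Rates 35/25/15/5%, power 80%, alpha 0.05, 250 and 275 per group (Sample size calculations); two-tailed Pearson chi-square (Data analysis); 1:1:1:1 allocation (Randomization and patient allocation). No multiplicity adjustment is applied.

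**Formulas.** With d = p1 − p2 = 0.10, pbar = (p1 + p2)/2, A = sqrt(2·pbar·(1 − pbar)) and B = sqrt(p1(1 − p1) + p2(1 − p2)):

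- size per group: n = (1.960·A + 0.842·B)² / d²
- power: Φ((d·sqrt(n) − 1.960·A) / B)

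**Step 1: reproduce the stated 250.** For 25% versus 15%, A = sqrt(0.320) = 0.5657 and B = sqrt(0.315) = 0.5612. Then n = (1.1087 + 0.4724)² / 0.01 = 249.98, so 250. This matches the article exactly.

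**Step 2: the same formula for letrozole versus personalized acupuncture.** For 35% versus 25%, A = sqrt(0.420) = 0.6481 and B = sqrt(0.415) = 0.6442. Then n = (1.2702 + 0.5422)² / 0.01 = 328.5, so 329. At 250 per group, d·sqrt(250) = 1.5811 and power = Φ((1.5811 − 1.2702)/0.6442) = Φ(0.483) = 68.5%. At 275 per group, d·sqrt(275) = 1.6583 and power = Φ(0.602) = 72.7%.

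**Step 3: all three adjacent pairs.**

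| Pair | n per group for 80% | Power at 250 | Power at 275 |
|---|---|---|---|
| Letrozole 35% vs personalized 25% | 329 | 68.5% | 72.7% |
| Personalized 25% vs fixed 15% | 250 | 80.0% | 83.6% |
| Fixed 15% vs placebo 5% | 141 | 96.3% | 97.6% |

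Exact enumeration of the chi-square test at 250 per group gives 68.5%, 80.3% and 97.0%, so the normal approximation is not the cause of the shortfall.

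**Step 4: can another method yield 250 for 35% versus 25%?**

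- Unpooled variance needs 326, arcsine 328 and the continuity correction 349.
- A one-sided 0.05 test needs 259 and has 78.8% power at 250, but the article specifies a two-tailed test.
- The four-group chi-square under the assumed rates needs only about 35 per group, so it is not where 250 comes from.

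**Step 5: dropout.** If the article's 10% dropout is carried through to 35% versus 25%, 329 becomes 362 by the article's own inflation (n × 1.10) or 366 by division (n/0.90), against the planned 275.

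**The case against.** The best defence is that Data analysis frames the primary analysis as differences among the four groups. As a single four-group test, its power at 250 per group under the assumed rates is above 99.9%. Two of the three adjacent contrasts also reach or exceed 80%. This stands, and it limits the point: a reader might infer that the trial's primary analysis as a whole is underpowered, and the document does not support that. It does not rescue the sentence in question, because 250 is a two-group figure and the 80% is offered for the whole ladder.

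Three other inferences go further than the document allows.

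- **That the under-powered contrast is the principal one.** It is listed first under Objectives, but nothing there ranks the hypotheses.
- **That a non-significant result will be taken as equivalence.** Nothing in the article proposes this. The hypothesis is that letrozole is superior, and Data analysis already plans relative risks with 95% confidence intervals for live birth.
- **That the letrozole rate is too high and power is therefore far lower still.** The article does move from a source in which women "received letrozole for 6 months was 36.3"% to "Thus, we hypothesize that the live birth rate is 35% for four cycles of letrozole treatments" with no stated allowance for the shorter treatment, so 35% is an assumption. But lowering letrozole alone while holding personalized acupuncture at 25% is arbitrary, since the article cites no source for the 25% either. If both rates fall and the 10-point gap is kept, power rises, as the 25% versus 15% pair shows. The document does not settle which would happen.

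Nor does the article promise 80% power for confirming all three hypotheses together, so it cannot be faulted for lacking it.

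**Conclusion.** The stated power is wrong for one of the article's own three adjacent live-birth hypotheses. For letrozole 35% versus personalized acupuncture 25%, power is about 68.5% at 250 per group. The chance of missing a true 10-point advantage is then about 31.5%, not the implied 20%. If all 275 per group contribute full outcome data, power is about 73%, still short of the claim.

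The result rests on the article's own rates, the unadjusted two-sided 0.05 level and the Pearson chi-square test. It does not depend on any view about the true four-cycle letrozole rate. Any multiplicity adjustment would lower the figure further. The error lies in the reported power; it does not show the design to be unsound.

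**What to change.** Keep 1100 women, the four arms and the test. In Sample size calculations, replace the single 80% claim with power per contrast at 250 evaluable per group:

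- about 68% for letrozole versus personalized acupuncture;
- 80% for personalized versus fixed acupuncture;
- about 96% for fixed acupuncture versus placebo letrozole.

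State that 250 was derived from the 25% versus 15% pair. A short note that the four-cycle 35% is an assumption informed by a 6-month figure would also help.

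In Data analysis, add that the letrozole versus personalized acupuncture risk difference will be reported with its 95% confidence interval and read against the 10-point minimum difference. At the assumed rates and 250 per group, the half-width is about 1.96 × sqrt(0.415/250) = 0.080, or 8 points, so the interval will show which differences remain plausible. This is a small addition to the relative risks already planned.

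The cost is a few sentences and one less favourable figure. Recruitment, procedures and treatment are unaffected.

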## Discussion

To the best of our knowledge, no previous study has investigated whether personalized acupuncture has the potential to increase the live birth rate in infertile women with PCOS. Our study is thus the first multicenter randomized controlled trial to compare the effects of personalized or fixed acupuncture with letrozole or placebo letrozole on live birth in infertile women with PCOS. The hypothesis is that letrozole is more effective than personalized acupuncture, that personalized acupuncture is more effective than fixed acupuncture, and that fixed acupuncture is more effective than placebo letrozole. Moreover, we hypothesize that personalized acupuncture is more likely than letrozole to reduce miscarriage rate and the risk of pregnancy complications.

Considering the treatment principle based on syndrome/pattern differentiation in TCM, the kidney, liver, and spleen are the top three zang-fu organs associated with the development of PCOS, and yin or yang deficiency is the essential cause, whereas pathological products such as phlegm are superficial [29]. Therefore, the therapeutic proposal should reinforce liver-kidney-yin deficiency, promote spleen-kidney-yang circulation, and resolve phlegm. We will divide the individual groups into two types according the theory of TCM as “liver-yin and kidney-yin deficiency” and “spleen-yang and kidney-yang deficiency.” This method is similar to that of actual clinical practice and can be used in future studies. The fixed acupuncture regimen is controversial based on the TCM theory of acupuncture.

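### The stated 80% power at 250 per group does not hold for letrozole versus personalized acupuncture, where the plan's own rates give about 68%

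*Protocol article*

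**What the plan says.** The Sample size calculations section first fixes the target: "We have chosen 10% as the minimal clinically detectable difference that is likely to change clinical practice". It then lists four rates in equal steps: "Assuming a 35% live birth rate with letrozole, a 25% live birth rate with personalized acupuncture", "a 15% live birth rate with fixed acupuncture" and "a 5% live birth rate with placebo letrozole". From these it concludes: "and an 80% power at a significance level of 0.05, we calculated that 250 subjects per treatment group were required". The 250 is raised to 275 for 10% dropout, giving 1100 women. Nothing limits the 80% to a particular pair of arms.

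The Objectives section sets out the comparisons that this size must serve. The first reads "Letrozole is more likely than personalized acupuncture to induce ovulation and to result in live birth". The second and third put personalized above fixed acupuncture, and fixed acupuncture above placebo letrozole, on the same outcomes. The Discussion restates the same ordering: "The hypothesis is that letrozole is more effective than personalized acupuncture, that personalized acupuncture is more effective than fixed acupuncture", and so on down to placebo.

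The Data analysis section names the Pearson chi-square test for live birth, by intention to treat, and sets a two-tailed significance level of 0.05. Allocation is 1:1:1:1.

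**The concern.** A fixed absolute difference does not have the same power at every level of the event rate. The variance of a proportion grows as the rate approaches 50%, so a 10-point gap is harder to detect between 35% and 25% than between 15% and 5%. A single power figure for three equally spaced pairs can be exact for at most one of them.

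The pair with the largest variance is letrozole versus personalized acupuncture. This comparison places acupuncture against the drug that the Background calls first-line therapy, and the abstract says the findings will inform whether personalized acupuncture can serve as an alternative treatment. If its power is well below 80%, a non-significant result is more likely than readers are told. A reader who trusts the stated power could take such a result as evidence that the two treatments perform alike, when the trial had a substantial chance of missing the very difference it assumed.

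**Working it through.** **Inputs, all from the protocol.** Rates 35%, 25%, 15%, 5%; power 80%; 250 per group, 275 after the dropout allowance (Sample size calculations). Two-tailed 0.05 and Pearson chi-square (Data analysis). Equal allocation (Randomization and patient allocation).

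**Formula.** For rates p1 and p2 with difference d and mean p̄, the size per group is

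n = [1.960·√(2p̄(1−p̄)) + 0.8416·√(p1(1−p1)+p2(1−p2))]² / d².

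**Reproducing the plan's figure (25% versus 15%, p̄ = 0.20).**
- √(2·0.20·0.80) = √0.320 = 0.5657
- √(0.1875+0.1275) = √0.315 = 0.5612
- n = (1.1087 + 0.4724)² / 0.01 = 249.98, so **250**

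The match is exact. The stated size is the requirement for personalized versus fixed acupuncture.

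**The first hypothesis (35% versus 25%, p̄ = 0.30).**
- √(2·0.30·0.70) = √0.420 = 0.6481
- √(0.2275+0.1875) = √0.415 = 0.6442
- n = (1.2702 + 0.5422)² / 0.01 = 328.5, so **329**

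**The third hypothesis (15% versus 5%, p̄ = 0.10).**
- √(2·0.10·0.90) = √0.180 = 0.4243
- √(0.1275+0.0475) = √0.175 = 0.4183
- n = (0.8315 + 0.3521)² / 0.01 = 140.1, so **141**

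**Power at a given n.** Power = Φ{[d√n − 1.960·√(2p̄(1−p̄))] / √(p1(1−p1)+p2(1−p2))}. For 35% versus 25% at 250: (1.5811 − 1.2702)/0.6442 = 0.483, and Φ(0.483) = 0.685.

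| Comparison | n per group for 80% | Power at 247.5 (275 less 10%) | Power at 250 | Power at 275 |
|---|---|---|---|---|
| Letrozole 35% vs personalized 25% | 329 | 68.1% | 68.5% | 72.7% |
| Personalized 25% vs fixed 15% | 250 | 79.6% | 80.0% | 83.6% |
| Fixed 15% vs placebo 5% | 141 | 96.2% | 96.3% | 97.6% |

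**Type II error for the first hypothesis at 250.** 100% − 68.5% = 31.5%, which is 31.5/20 = 1.57 times the stated 20%. At 275 it is 27.3%, or 1.37 times.

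**Detectable difference.** Holding letrozole at 35% and n at 250, the formula gives 80% power at d = 0.1138, that is, 35% against about 23.6%. The detectable gap is 11.4 points, not 10.

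**Does another method rescue the figure?**
- Exact binomial power of the uncorrected Pearson test at 250 for 35% versus 25%: 68.5%.
- Size for this pair by other two-sided formulas: unpooled 326, arcsine 328, continuity-corrected 349.
- One-sided 0.05: this pair needs 259 (78.8% power at 250; 82.1% at 275). That contradicts the two-tailed rule, and personalized versus fixed would then need 197, so it is not where 250 came from.
- Four-group chi-square: about 35 per group gives 80% power, so 250 was not derived from it. A significant overall test also does not show which arm beats which.

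**The case against.** Four points can be made for the plan.

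**The analysis set is 275, not 250.** The primary analysis is by intention to treat, and dropouts are to be included through imputation. On that view the first hypothesis has 72.7% power. This is fair as an upper limit, but imputation does not fully restore lost information. The honest range is about 68% to 73%, and both ends are below 80%.

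**No estimate is biased and the type I error is unaffected.** This is true. The other two comparisons are also adequately powered, including personalized versus fixed acupuncture, which bears most directly on the trial's novelty. The fault is in a stated operating characteristic, not in the test or the data. It still concerns the primary outcome and a named objective.

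**The hypotheses are not ranked, and no equivalence claim is planned.** This also stands: being listed first does not make the letrozole comparison the leading test, and the misreading of a null result is a risk, not a plan. Relative risks with 95% confidence intervals are already promised, which partly guards against it.

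**Nobody claims 80% power for the whole ordering.** Correct. The chance that all three pairwise tests are significant is about 49% at 250 per group (by simulation), but the protocol does not define success that way. The figure is useful context for the ordering restated in the Discussion and is not a second error.

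**Conclusion.** The concern holds. On the protocol's own rates, test and significance level, 250 women per group give 80% power for personalized versus fixed acupuncture and more than that for fixed acupuncture versus placebo letrozole. For letrozole versus personalized acupuncture they give 68.5%, rising to 72.7% only if every one of the 275 randomized women per group is evaluable. The shortfall is 79 evaluable women per group (329 − 250). The sample size was set on the middle pair, and its power was reported for the whole design.

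The conclusion assumes that the four planning rates are true and that each pair is tested at two-sided 0.05 without adjustment for multiple comparisons. An adjustment would lower the power further: at 0.05/3, which is illustrative and not in the protocol, the first hypothesis would have about 52% at 250 per group. The result does not depend on the choice among standard two-sided formulas.

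**What to change.** Replace the single power statement in Sample size calculations with one by pair, for example:

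*With 250 evaluable women per group and a two-sided 0.05 test, power is 80% for personalized versus fixed acupuncture (25% vs 15%), about 68% for letrozole versus personalized acupuncture (35% vs 25%) and 96% for fixed acupuncture versus placebo letrozole (15% vs 5%). For letrozole versus personalized acupuncture, the difference detectable with 80% power is 11.4 percentage points. If all 275 women per group are evaluable, power for that comparison is about 73%.*

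Add one sentence to Data analysis: a non-significant result for letrozole versus personalized acupuncture will be reported as inconclusive, with its confidence interval, and not as evidence of similar efficacy.

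The cost is one paragraph and a less favourable figure for the first hypothesis. No patients, arms, outcomes or tests change. Restoring 80% for this pair in equal groups would instead take 329/0.9 = 366 per group, or 1464 women in total, 364 more than planned. With recruitment open since August 2018 that is a separate decision, and the correction does not depend on it.
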